
### Course outcomes

At the end of the training, participants are anticipated to be able to describe components of their current local trauma system (trauma capacity), describe barriers to effective trauma care in their settings, suggest areas for performance improvement, demonstrate concepts of primary survey and secondary survey, know when to make a timely decision to consult or transfer (referral) for definitive care, and understand the link between lower hospital facilities and regional trauma centers. These goals have been set apriority in accordance with the committee on trauma^27^. The participants will complete a paper based pretraining trauma related MCQs before and at 3 months after the training. The method of data collection will remain the same with a target data completion rate of 100% for every series. The prepost training MCQs will be marked by two independent consultant surgeons who are not part of the research team. The marking team will be blinded by what is pretraining or post-training. Since the answers and marking guide are standardized, we anticipate an inter-rater agreement of 100%.

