### Source of data and study settings

This study will be conducted at three regional referral and teaching hospitals in Uganda, including Kiryandongo, Jinja, and Hoima. These facilities have similar characteristics in the sense that they all serve as internship and residency sites for graduating general doctors, surgery residents and as teaching sites for the Kampala International University Medical School. In co-operation with local surgeon consultants, each of these tertiary hospitals offers specialized services including emergency surgery for injured patients such as those with neuro, orthopedic, and general trauma. The key staff in the surgery and trauma departments include at least a specialist surgeon, a master’s resident, intern doctor/nurse and support staff who work with other departments such as occupational therapy, physiotherapy, and rehabilitation to offer 24 h multidisciplinary services to the injured patients. In addition, each of these facilities receive undergraduate medical trainees including those studying for Bachelor of Medicine and Bachelor of Surgery, Bachelor of Nursing Sciences, and Bachelor of Clinical Medicine degrees here being collectively referred to as medical trainees. The trainees rotate on a 1–5 months basis in major clinical disciplines such as surgery amongst others. Furthermore, each of these hospitals are in proximity with the regional district police headquarters which offers complementary services such as legal guidance on traffic crashes, third party compensation claims and issuance of ‘police form 3A’ for the examination of injured persons. Patients sustaining either intentional or unintentional injuries are immediately encouraged to report to the police for investigations and often police attend to such patients as first-responders at the crash scenes.

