### Training procedure, team construct, and course implementation

On average 12 (6–24) training sessions will be conducted per site between 28th of September 2019 and 28th of November 2023. Cohorts of participants will be enrolled every after 3 months to strike a balance between the average duration of surgical internship deployment by the Ugandan ministry of health which lasts 1–5 months, and the surgery clinical rotations for medical students which lasts 2 months. Furthermore, the effects of the training are presumed to ‘decay’ after this period and the authors project to realize the targeted sample size based on the 3 months interval. However, permission will be sought from the ethical committee to extend the study in case the target sample is not obtained during the approved duration of the study. The mode of delivery and content of the RTTDC training will not be modified. The training will be advertised by hospital administrators and class representatives and eligible participants will be recruited based on first come first serve. The training dates will be selected to suit the designated days for clinical grand rounds and/ or continuous professional development sessions so as not to interfere with the university and hospital daily schedules. The investigators will use student unique numbers from university hospital administrators’ database to randomly assign recruited participants into teams and to ensure that each participant is recruited once. The participating law enforcement professionals who will show up for the training will pick ballot papers randomly to be assigned to the already created medical trainee teams. The chief trainer will be a chief surgeon (HL) who attended the RTTDC instructor course. The surgeon will coach two co-trainers who are master of surgery residents undertaking a traumatology rotation, at the participating hospitals to make a total of three trainers. Since the program is aimed at capacity building, and residents directly supervise interns in Uganda, the research and ethics board approved training of residents as opposed to consultants not to over strain the skeleton specialized staff at the study sites. Interns and residents contribute to 75% of the health workforce in public hospitals in Uganda^8^. The program will be designed for two days, targeting 30 participants with a trainer: trainee ratio of 1:10, which is the maximum permissible for each training session according to the committee on trauma of the American college of Surgeons. For each team task, participants will be grouped into teams of five to role play a surgeon, surgeon assistant/intern, an anesthesiologist/anesthetic assistant, an allied health professional (emergency room nurse/laboratory/imaging personnel), and a rescue police (representing paramedics in Uganda’s settings).

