### Study population

We shall target nursing students and medical students/interns who are often the first contacts to trauma patients in hospital settings and road traffic law enforcement professionals who are often involved in transportation of such patients to hospitals. The accessible population will be those medical trainees/interns completing the surgery rotation during the study period and police officials assigned to complete the training by virtue of their roles.

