### Sample size estimation

According to the respective hospital administrators, a total of 1500 medical trainees had been received at the three participating hospitals during the academic year 2018/2019, which preceded the study. Using the hypergeometric formula in equation 1 for determining sample size in smaller populations,

(1)
$$n=\frac{Nz^{2}\mathrm{pq}}{\left[E^{2}\left(N-1\right)+z^{2}\mathrm{pq}\right]}$$

where:

*N* (population size) =1500

Z=1.96 assuming 95% CI.

P and Q are population proportions that will approve or disapprove the promulgation of rural trauma team development training, each assumed to be 50% since these proportions are unknown

E=value of accuracy of the sample proportions (alpha= 0.05) at 95% CI

*n* (sample size)=307. Since, we plan to retain this same cohort of trainees after 3 months of follow-up for purposes of their incorporation into real-world rural trauma teams during the second phase of the project which will run for the next 4 years from the time of postcourse evaluation, and with a projected 10.25% annual loss to follow-up and nonresponse, we shall add 41% to increase internal validity for the entire 4-year period, thus the final minimum sample size for medical trainees will be 433.

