### Statistical analysis

The data will be exported from REDCap to Stata version 15.0 for analysis (StataCorp. 2017. Stata Statistical Software: Release 15. College Station, TX: StataCorp LLC).

We shall test the data for normalcy using the Shapiro–Francia test and normal histogram curves at 95% CI, regarding *P*<0.05 as statistically significant.

If the data are normally distributed, the difference in pretraining and post-training mean scores will be compared using one way analysis of variance (ANOVA) test otherwise nonparametric Friedman test will be used to compare the scores as a measure of knowledge retention, assuming a null hypothesis of no difference. Box plots will be used for data presentation to offer a succinct visual summary of data distribution.

Furthermore, we shall perform Wilcoxon signed rank nonparametric test to examine the difference in the effect the training has on MCQ scores of the various cadres of participants aggregated (3rd year, 5th year, and interns). The median scores for various groups and their corresponding interquartile range will be reported.

The statistical difference in rank sums regarding desirability and relevance of various course themes will be compared between participating cadres using a nonparametric Kruskal–Wallis (H) test.

Lastly, time series regression (ARIMA) models will be used to test for autocorrelation trends in MCQ performance over the study period for the various medical trainee groups.

All the analyses will be performed using Stata 15.0. (StataCorp. 2017. *Stata Statistical Software: Release 15.* College Station, TX: StataCorp LLC); at 95% CI, regarding a 2-tailed *P*-value <0.05 as statistically significant.

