### Participant recruitment workflow

The potentially eligible participants will be registered, briefed, and educated about the study 2 weeks prior to the training; and availed links to the educational materials. Consented participants will be recruited for this 2-day event. On the agreed first day of the training, interns and medical trainees will complete pretraining MCQs during the first 40 min in ‘an exam-like’ supervise environment, followed by assignment into random groups. The training will be divided into four modules, that is, (i) introduction to rural trauma systems, primary and secondary survey, (ii) case scenarios, (iii) trauma communication, and (iv) patient safety and process improvement. Each module will be allocated 2 h to make a total of 8 h of ‘continuing medical education’, which is the maximum allowable by the committee on trauma of American College of Surgeons. The first half of the course modules will be delivered during Day 1 and the remaining half on Day 2 of the training. The training for all teams will take place between 9:00 am and 15:00 pm and the venue will be the designated spacious multimedia surgical simulation room located at each of the training hospitals. There will be coffee breaks of 45 min between each 2 h session on each day of the training. The PI will cater for the coffee budget to enhance attendance and time efficiency. The participants will maintain their teams throughout training days. Study participants will be given overall team performance feedback after the last module and each study subject will be asked to complete a 15 min course evaluation form regarding acceptability and relevance of the training at the end of Day 2. Subsequently, trainee participants will be followed up after 3 months (90 days) from Day 1 of the training to complete a 40 min post-training trauma based MCQs in ‘an exam-like’ supervised environment as shown in Figure 1.

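### The pre/post MCQ comparison is a one-way ANOVA although the same trainees sit both tests: it wastes the pairing and, if some miss day 90, lets the two means describe different people

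*Protocol article*

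**What the plan says.** The first specific objective compares pre- and post-course scores in medical trainees. Course outcomes and Participant recruitment workflow have the same trainees sit both tests: "trainee participants will be followed up after 3 months (90 days) from Day 1 of the training". Training procedure adds that student numbers are used so that each trainee is recruited only once. The design is therefore within person.

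For the analysis, Statistical analysis states: "the difference in pretraining and post-training mean scores will be compared using one way analysis of variance (ANOVA) test otherwise nonparametric Friedman test". A normality check chooses between the two. The signed-rank test appears only in a further analysis of the cadres.

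On follow-up, Course outcomes states: "The method of data collection will remain the same with a target data completion rate of 100% for every series". Sample size estimation enlarges the sample "with a projected 10.25% annual loss to follow-up and nonresponse", and the ethics section allows withdrawal.

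On timing, Training procedure gives "the surgery clinical rotations for medical students which lasts 2 months" and, for interns, "the average duration of surgical internship deployment by the Ugandan ministry of health which lasts 1–5 months". Study population says: "The accessible population will be those medical trainees/interns completing the surgery rotation during the study period".

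**The concern.** One-way ANOVA on two sets of scores is the two-sample comparison. It does not know that a pre-test and a post-test belong to one person. Two things follow.

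- **With every score present**, the estimated gain is right, but its standard error is too large whenever the two scores are positively correlated. Power for the first objective is lost for no return.
- **With some post-tests absent**, nothing in the named test ties the two means to the same trainees. A trainee with only a pre-test can count in the pre mean and not in the post mean. Friedman needs both scores, so it would leave that trainee out. The normality check would then decide whom the result describes, as well as which test is run.

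The calendar makes absent post-tests plausible, because the sitting is due after a student's 2-month surgery rotation has finished.

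**Working it through.** **Inputs from the protocol.** 433 trainees; post-test at 90 days; student rotation 2 months; intern deployment 1–5 months; loss 10.25% a year; a 20-item MCQ, so one item is 100/20 = 5 percentage points.

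**Assumed, because the protocol gives none.** SD 15 points; pre/post correlation 0.5; true gain 0 or 2 points; baseline deficit of non-returners 5 or 10 points; any loss above the protocol's own rate.

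**1. The protocol's sample size.** 1500 × 1.96² × 0.25 / (0.05² × 1499 + 1.96² × 0.25) = 1440.6 / 4.7079 = 306.0 (stated: 307). Then 4 × 10.25% = 41%, and 307 × 1.41 = 432.9, so 433 is reproduced. The number serves an approval proportion and already allows for loss. It does not rest on full completion, and it says nothing about power for MCQ scores.

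**2. The calendar.** Two months is 60 or 61 days. Even if training falls on the first day of a student's rotation, day 90 comes 29–30 days after it ends.

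**3. Complete data.**
- SE used by one-way ANOVA: 15 × √(2/433) = 1.019. It rejects when the difference exceeds 1.96 × 1.019 = 1.998.
- True SE of the mean change: 15 × √(2 × (1 − 0.5)/433) = 0.721.
- Rejection under no change: 1.998/0.721 = 2.77, so about 0.6% instead of 5% (0.4–0.6% in simulation).
- Power for a 2-point gain: ANOVA (2 − 1.998)/0.721 ≈ 0, so 50%; paired 2/0.721 − 1.96 = 0.81, so 79%.
- At correlation 0.3 the paired power is 65%, and at 0.7 it is 95%. The ANOVA stays near 50%.

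**4. Some post-tests missing.** Let m be the fraction missing and d the amount by which non-returners score lower at both sittings. With no true gain, the unmatched difference is m × d. The protocol's rate over three months gives 10.25%/4 = 2.6%, about 11 of 433. Rejection rates are from 2000 simulated trials with no true gain.

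| Loss m | False gain, d = 5 | False gain, d = 10 | ANOVA rejects, d = 10 |
|---|---|---|---|
| 2.6% | 0.13 | 0.26 | 1% |
| 10.25% | 0.51 | 1.02 | 7–9% |
| 20% | 1.0 | 2.0 | about 43% |
| 40% | 2.0 | 4.0 | about 96% |

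In this setting, using the same people in both means gives no bias and about 5% rejection. At d = 5 and 20% loss, ANOVA rejects in only 7–8%.

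**5. Loss that depends on the pre-test score itself.** Suppose lower pre-test scorers are likelier to miss day 90 (logistic in the standardised pre-test score, slope 1). At about 13%, 24% and 33% loss:
- the unmatched gain is +0.9, +1.5 and +2.1;
- the complete-pair gain is −0.9, −1.5 and −2.1;
- a likelihood-based repeated-measures estimate using all scores is about 0.

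That last estimate is not a cure-all. In the setting of step 4, its bias is m × d × (1 − 0.5), half that of the unmatched comparison. If loss is unrelated to score, no method is biased.

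**The case against.** Several points on the other side are sound.

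- **The 100% figure.** A reader might infer that the plan assumes full completion. It does not: the text calls it a target, no calculation uses it, and the sample size allows for loss. The 10.25% is also tied to a four-year second phase, so the two figures do not strictly contradict each other.
- **The rotation.** A reader might infer that students are lost once the rotation ends. The protocol does not say so. "The trainees rotate on a 1–5 months basis in major clinical disciplines such as surgery amongst others", so a trainee may simply be in another department. The inclusion criteria also admit students who have already completed the rotation, and interns may be deployed for up to 5 months. The timing makes absence plausible and no more.
- **The missing-data rule.** An article commonly leaves this to the full protocol or analysis plan, so its absence is not the error.
- **Pre-only records.** The text does not say that they enter the ANOVA, and the Friedman fallback suggests that a repeated-measures analysis may have been intended.
- **Size.** At the protocol's own loss rate the bias is about a twentieth of one MCQ item.

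What remains is the test as named. A one-way ANOVA is the wrong analysis for paired scores even with no loss, and it does not keep the two means on the same people if there is any. If a repeated-measures analysis was meant, the text should say so.

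**Conclusion.** The point holds for the stated method and should be corrected. One-way ANOVA ignores the pairing. With complete data this costs power, about 50% against 79% under the assumed SD, correlation and 2-point gain, and it makes a false positive less likely.

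The bias is conditional. It needs missed post-tests and a link between missing and score. It is about 0.3 points at 2.6% loss, and 1 to 2 points at 10 to 20% loss, with a 10-point deficit. That deficit and the higher loss rates are assumptions, and the sign reverses if higher scorers are the ones lost. The documents do not support saying that the gain is biased, only that the stated test leaves it open to bias.

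**What to change.** In Statistical analysis:

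1. Replace one-way ANOVA with a within-person comparison. Either analyse each trainee's own change (paired t-test), or fit a repeated-measures mixed model to all available scores, which also handles loss that depends on the pre-test score. Name which is primary.
2. Use the signed-rank test as the nonparametric counterpart in place of Friedman, which with two sittings uses only the direction of each change. With the paired change as primary, both routes then describe the same trainees. If the mixed model is primary, say that the signed-rank result covers complete pairs only.
3. Report baseline scores of trainees with and without a post-test, because complete pairs alone do not remove selective loss.
4. As an optional sensitivity check, give each non-returner a post-test equal to the pre-test.

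In Course outcomes, it would help to state an expected 90-day return rate beside the 100% target.

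The cost is a few sentences and minor extra analysis, with no new data.

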### Study population

We shall target nursing students and medical students/interns who are often the first contacts to trauma patients in hospital settings and road traffic law enforcement professionals who are often involved in transportation of such patients to hospitals. The accessible population will be those medical trainees/interns completing the surgery rotation during the study period and police officials assigned to complete the training by virtue of their roles.

### Sample size estimation

According to the respective hospital administrators, a total of 1500 medical trainees had been received at the three participating hospitals during the academic year 2018/2019, which preceded the study. Using the hypergeometric formula in equation 1 for determining sample size in smaller populations,

(1)
$$n=\frac{Nz^{2}\mathrm{pq}}{\left[E^{2}\left(N-1\right)+z^{2}\mathrm{pq}\right]}$$

where:

*N* (population size) =1500

Z=1.96 assuming 95% CI.

P and Q are population proportions that will approve or disapprove the promulgation of rural trauma team development training, each assumed to be 50% since these proportions are unknown

E=value of accuracy of the sample proportions (alpha= 0.05) at 95% CI

*n* (sample size)=307. Since, we plan to retain this same cohort of trainees after 3 months of follow-up for purposes of their incorporation into real-world rural trauma teams during the second phase of the project which will run for the next 4 years from the time of postcourse evaluation, and with a projected 10.25% annual loss to follow-up and nonresponse, we shall add 41% to increase internal validity for the entire 4-year period, thus the final minimum sample size for medical trainees will be 433.

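### The 433 target adds 41% to 307 instead of dividing by the retained fraction, so at the protocol's own loss rate it leaves about 255 to 281 trainees at 4 years, not 307

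*Protocol article*

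**What the plan says.** Under Sample size estimation, the protocol article applies a finite-population formula for one proportion: the share of trainees who would approve wider roll-out of the training. It reports a base of 307. It then says that the same cohort is to be kept for a second phase of 4 years, "with a projected 10.25% annual loss to follow-up and nonresponse". On that basis, "we shall add 41% to increase internal validity for the entire 4-year period, thus the final minimum sample size" for medical trainees is given as 433.

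The figure is used. Under Sampling methods, the site allocations (321, 65 and 47) sum to 433.

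**The concern.** An allowance for loss should be large enough that, once the projected loss has happened, the required number is still there. That means dividing the required number by the fraction expected to remain. Multiplying by one plus the loss fraction always falls short, and the gap widens as the loss grows. At 41% it is substantial.

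What is at stake is the number of trainees carried into the second phase. Someone planning that phase from this section would expect about 307, but the section's own loss rate implies fewer.

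**Working it through.** **Inputs, all from Sample size estimation**
- Population: "a total of 1500 medical trainees had been received at the three participating hospitals", so N = 1500.
- "Z=1.96 assuming 95% CI", so z = 1.96.
- p and q: "each assumed to be 50% since these proportions are unknown".
- Precision: E = 0.05.
- Base sample size: 307.
- Annual loss and nonresponse: 10.25%.
- Period: 4 years.

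**Reproducing the plan's figures**
- Base: 1500 × 1.96² × 0.25 / (0.05² × 1499 + 1.96² × 0.25) = 305.996. This agrees with 307 to within one person, and 307 is used below.
- Allowance: 4 × 10.25% = 41%.
- Target: 307 × 1.41 = 432.87, rounded up to 433.

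Other rules do not give 433: 307 / 0.59 gives 521, 307 / 0.8975⁴ gives 474, and 307 × 1.1025⁴ gives 454. The 433 therefore comes from adding 41%.

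**What 433 leaves at 4 years**

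The stated annual rate can be read in two ways.

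| Reading of 10.25% a year | Fraction retained | Left from 433 | Enrolment needed to keep 307 | Shortfall in target |
|---|---|---|---|---|
| Summed, as the protocol does | 1 − 0.41 = 0.59 | 433 × 0.59 = 255.5 | 307 / 0.59 = 520.3, so 521 | 521 − 433 = 88 |
| Compounded | 0.8975⁴ = 0.6488 | 433 × 0.6488 = 280.9 | 307 / 0.6488 = 473.2, so 474 | 474 − 433 = 41 |

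The target would keep 307 only if total loss were at most 1 − 307/433 = 29.1%. Compounded, that is about 8.2% a year, below the projected 10.25%.

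**What 433 gives for this study's own end points**
- Approval proportion at the end of Day 2, with p = 0.5 and the finite-population correction: 1.96 × √[(0.25/433) × (1500 − 433)/1499] = 0.0397, or about ±4.0 points. This is tighter than the ±5 used for sizing.
- Knowledge test at 3 months: the protocol gives no 3-month loss rate. If the annual loss is assumed to accrue evenly, 433 × 0.8975^0.25 = 421.5 or 433 × (1 − 0.1025/4) = 421.9 remain, about 421 to 422.

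**The case against.** The strongest reply is that nothing in this study depends on having 307 trainees at year 4. The formula sizes an estimate of approval. Participant recruitment workflow places the acceptability and relevance form at the end of Day 2, and the only later trainee outcome is the 3-month test. The follow-on work described under Study strengths and limitations is a cluster randomised trial of clinical time efficiency and patient outcomes, which a one-proportion formula for trainee approval would not size. Nor does the section say outright that 307 must remain at year 4; that is inferred from the stated purpose of the allowance. All of this stands, and it limits the weight of the point. It does not rescue the arithmetic, because the only reason given for the 41% is loss over those 4 years, and it does not cover that loss.

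A reader might go further in three ways that the protocol does not support:
- **Lost precision at year 4.** The margin formula gives about ±5.6 points at 255 and ±5.3 at 280, so one might say that the promised ±5 is missed. No passage plans to estimate the approval proportion at year 4, so no planned estimate loses precision.
- **A conflict with full completion.** Course outcomes sets a "target data completion rate of 100% for every series". This is an operational goal for the pre-training and 3-month tests. Aiming for full completion while allowing for loss is ordinary practice.
- **A wrong base figure.** The formula rounds up to 306, not 307. The difference is one person in the safe direction and is immaterial.

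**Conclusion.** The target is wrong as an allowance for the loss it names. Under either reading of the annual rate, 433 falls short: about 255 (summed) or 281 (compounded) remain at 4 years, against a base of 307. That is 26 to 52 fewer, or roughly 9% to 17%.

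The conclusion rests on the protocol's own 10.25% a year and on reading the 41% as meant to preserve the base number.

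Severity is minor. One might infer that the present study is too small, but the documents do not support that. The Day 2 approval estimate has a margin of about ±4.0 points with 433, and the 3-month test would keep well over 307 trainees (about 421 to 422 under the even-accrual assumption). Only the number stated or implied for the second phase is affected.

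**What to change.** Keep 433 and correct what is said about it under Sample size estimation:
- State that, at 10.25% loss a year, 433 enrolled is expected to leave about 255 trainees (losses summed) to 281 (losses compounded) after 4 years, and say which reading is meant. Alternatively, state that 307 need not be retained for the second phase.
- If useful to later planning, note that keeping 307 would have needed 521 (summed) or 474 (compounded).
- State that 433 gives about ±4.0 points for the approval proportion at the end of Day 2. If a 3-month number is quoted, label it as assuming that the annual loss accrues evenly.

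The cost is a few restated figures and a less favourable long-term retained number. No added enrolment is asked for; Study updates anticipates the last participant by 28 November 2023, before the article's publication date of 8 February 2024. No analysis or end point of this study changes.
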